In Malawi, communities struggle to sustain 100% latrine coverage after attainment of Open Defecation Free (ODF) status [21]. This has been attributed to a number of factors, including the lack of involvement of marginalized and disadvantaged people, the use of low-quality building materials, lack of technical support, and improper program implementation [14,22]. To achieve high and sustained latrine coverage and behavior change, it is essential to address all physical and contextual factors that directly relate to long-term CLTS success. The Government of Malawi adopted CLTS as one of its official approaches to sanitation in 2008 [23]. The Government formally adopted the CG model in 2011 as an operational framework for the Scaling Up Nutrition (SUN) Strategy [24]. However, little is known about how effective the CG model can be in promoting wider community health benefits, such as improved sanitation. Models to promote sustained reductions in open defecation and improved sanitation outcomes through a combination of behavior-centered intervention need to be tested and adopted to support long-term positive health outcomes.

This study aims to assess the effectiveness of CLTS combined with the CG model on sanitation coverage and use and hygiene behaviors in Chiradzulu District, in rural Malawi, compared to CLTS alone or with no intervention. The study objectives are to assess: (1) how the 2 interventions compare with one another for improving sanitation coverage and use, and (2) whether the 2 interventions are individually more effective than no intervention at all.

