### Sample Size

Sample size calculations were based on the minimum detectable effect (MDE) to assess changes in sanitation coverage, the primary outcome measure, at the project end line. Data for all parameters used in sample size calculations were drawn from the baseline survey conducted by World Vision before the implementation of the W4E project between January and April 2021. For the MDE calculation, we assumed a 2-tailed test with a significance level of 0.05 and a power of 0.8. We assumed a conservative intracluster coefficient of 0.1 [30]. As baseline data indicates that the average percentage of households with at least unimproved sanitation coverage across Chiradzulu District was 67%, power calculations assumed a total enrollment of 20 intervention clusters in each TA receiving interventions and 30 clusters selected from the control arm of the study. Assuming an average of 20 households surveyed per selected cluster results in an MDE of 0.136 or an average difference of 13.6 percentage points in sanitation coverage (relative change in coverage of 19%) between either arm of intervention clusters and the control cluster. Therefore, the study aims to recruit a total of 1400 households (CLTS+CG: n=400; CLTS only: n=400; Control: n=600; Figure 2) at each data collection round.

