### Analysis

Statistical analysis will be carried out at the individual or household levels with appropriate adjustments for clustering within villages (and within households for individual-level outcomes). Data will be analyzed according to the TA and intervention assignment irrespective of whether the intervention was taken up fully, partly, or not at all. Since this is an effective study, only an intention-to-treat dataset will be maintained.

The primary estimates of the effectiveness of the intervention on primary and secondary outcomes will be based on a difference-in-difference analysis and models adjusted for design variables alone (TA, village population above or below TA-specific median); a fixed effect for village size (above or below the median) will be included in the model. All models will include a dummy variable for the treatment arm (ie, CLTS, CLTS+CG, or control) and data collection round (baseline and end line) as well as the interaction term of those 2 variables.

To account for the clustering of observations, hierarchical mixed-effects models will be used for all analyses. For household-level outcomes or outcomes where there is only one respondent per household, mixed effects models will account for clustering by including a random effect at the village level. For outcomes with multiple respondents or data points per household (specifically sanitation use, and hand washing behavior), an additional random effect will be added at the household level.

All analysis of primary and secondary outcomes will be based on the difference-in-difference approach. The regression coefficient of the interaction term between the treatment arm and the data collection round will be used as the primary effect measure. For binary outcomes measure, we will use melogit with robust SEs and regression coefficients exponentiated to estimate an odds ratio (OR). For continuous outcomes, we will use meglm, with identity link and Gaussian family.

The results will be presented with 95% CIs. Analyses will report on ORs and 95% CIs of each treatment arm compared to the control as well as the CLTS alone compared to CLTS+CG. Secondary outcomes include the following:

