## Discussion

### Anticipated Findings

Given that CLTS alone is reportedly not effective at ensuring sustained uptake of sanitation and hygiene behaviors, we test the hypothesis that the CLTS+CG intervention will be more effective at improving sanitation coverage in a rural area of Malawi than the CLTS intervention alone, and also relative to the no intervention arm. Studies have shown the effectiveness of using the CG model in promoting community health interventions, mainly nutrition programs [19,34-37]. However, there is limited evidence on the impact of interventions integrating CLTS and the CG model to address this gap, we tested an intervention that integrates the CG model into the standard CLTS approach. The CG model is a community-level government-recognized approach that can potentially support the already existing informal natural leaders in the delivery of CLTS, both pre- and post-ODF status attainment. This could strengthen the sustainability of CLTS as CG members are trained to continuously monitor groups of households post-ODF attainment, whereas Natural Leaders only follow up with households until the community has achieved ODF status [9,11,38,39]. Results from this trial will provide evidence on the extent to which the CLTS+CG approach is effective at improving sanitation and hygiene practices in the W4E program area compared to CLTS alone and no intervention, as well as inform implementing partners on future interventions in Chiradzulu District, Malawi.

Our baseline results indicate that the study is conducted in a rural area where the literacy level is moderate and the quality of housing relatively poor. Some households had no latrines, while traditional unimproved latrines (eg, pit latrines without slab), which are prone to collapse during the rainy season, are common. Relatively high sanitation coverage in the communities indicates the short-term success of CLTS, however, other TAs in Chiradzulu District have reverted to OD after achieving ODF status. Thus, the district provided a suitable environment for this study to assess alternative approaches for promoting sustainable sanitation interventions.

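### The stated MDE of 13.6 points is an end-line comparison of one arm with control; none is given for the planned difference-in-difference or for CLTS+CG v CLTS

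*Protocol article*

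**What the plan says.** The Sample Size section of the protocol article ties the calculation to sanitation coverage at end line. Its inputs are these:

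- Error rates: "we assumed a 2-tailed test with a significance level of 0.05 and a power of 0.8".
- Clustering: "We assumed a conservative intracluster coefficient of 0.1", with 20 households per village.
- Reference level: the average share of "households with at least unimproved sanitation coverage across Chiradzulu District was 67" percent.
- Villages: "20 intervention clusters in each TA receiving interventions and 30 clusters selected from the control arm of the study".

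The result is an MDE of 0.136, glossed as a "relative change in coverage of 19%) between either arm of intervention clusters and the control cluster". The target of 1400 households per round is drawn from it.

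The Analysis section sets a different estimator: "The regression coefficient of the interaction term between the treatment arm and the data collection round will be used as the primary effect measure". It reports each arm against control and also CLTS against CLTS+CG.

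The Introduction lists as its first objective "how the 2 interventions compare with one another for improving sanitation coverage and use". Anticipated Findings opens with the hypothesis that the "CLTS+CG intervention will be more effective at improving sanitation coverage in a rural area of Malawi than the CLTS intervention alone".

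**The concern.** The MDE that justifies the sample size describes neither the estimator to be used nor the contrast the trial puts first.

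- **Estimator.** A difference-in-difference uses two rounds, so its precision depends on how strongly a village's coverage at baseline correlates with its coverage at end line. The calculation has no such term.
- **Contrast.** CLTS+CG v CLTS has 20 villages a side instead of 20 and 30, so at the same starting level its MDE is larger than the one published.
- **Relative change.** The percentage does not follow from the stated base.

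A reader who meets a null result, above all on CLTS+CG v CLTS, would naturally measure it against 13.6 points. That figure was not calculated for that comparison or for that model.

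**Working it through.** **Inputs (Sample Size section).** Two-sided alpha 0.05 (z = 1.960), power 0.80 (z = 0.842), ICC 0.1, m = 20 households per village, p = 0.67, 30 control villages and 20 per intervention arm. The design effect is 1 + 19 × 0.1 = 2.9.

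**1. The plan's figure.** Effective sizes are 600/2.9 = 206.9 and 400/2.9 = 137.9. With q = p + d and p̄ the weighted mean coverage, solve

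d = 1.960·√[p̄(1−p̄)(1/206.9 + 1/137.9)] + 0.842·√[p(1−p)/206.9 + q(1−q)/137.9].

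At q = 0.8058, p̄ = 0.7243 and the two roots are 0.0491 and 0.0469. The right-hand side is 0.1358, which matches 0.136. No second round enters.

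**2. Relative change.** 0.136/0.67 = 20.3%. For 19% the base would have to be 0.136/0.19 = 71.6%, which the article does not give.

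**3. CLTS+CG v CLTS at end line.** The same formula with 137.9 v 137.9 gives 14.7 points from 67%. Power for 13.6 points is 73%. If CLTS had already reached 80.6% (67 + 13.6), the MDE for the addition of care groups would be 11.5 points, to 92.1%.

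**4. Difference-in-difference.** The between-round village correlation r is not given, so I take 0 to 1 as an assumption. Households are treated as independent between rounds, as in the planned household-level model. The correlation between a village's two observed means is then c = m × ICC × r/2.9 = 2r/2.9. Write s = p(1−p) = 0.2211, t = q(1−q), with k_C and k_T the numbers of villages in the comparator and the intervention arm. Three of the four cells are at 67% and one at q:

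V = (2.9/20)·{2s(1−c)/k_C + [s + t − 2c√(st)]/k_T}, MDE = (1.960 + 0.842)·√V.

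- r = 1, 30 v 20: c = 0.690, q = 0.781, V = 0.145 × (0.00457 + 0.00620) = 0.00156, so MDE = 2.802 × 0.0395 = 0.111.
- r = 0, 30 v 20: c = 0, q = 0.860, V = 0.145 × (0.01474 + 0.01707) = 0.00461, so MDE = 2.802 × 0.0679 = 0.190.

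| r | Arm v control (30 v 20) | CLTS+CG v CLTS (20 v 20) |
|---|---|---|
| 1 | 11.1 | 12.2 |
| 0.8 | 13.2 | 14.5 |
| 0.5 | 15.7 | 17.3 |
| 0 | 19.0 | 20.9 |

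Against control, the MDE equals 13.6 points at r of about 0.75. A simpler covariance term moves these values by about 0.1 point at most.

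**5. Observed baseline (Table 2, all categories except no facility).** Control (26+55+483)/600 = 94.0%; CLTS+CG (43+64+278)/400 = 96.3%; CLTS (28+30+333)/400 = 97.8%. The room to rise is 6.0, 3.75 and 2.25 points. On this definition a 13.6-point rise cannot occur. A difference-in-difference of that size would need control coverage to fall by at least 13.6 − 3.75 = 9.85 points (against CLTS+CG) or 13.6 − 2.25 = 11.35 points (against CLTS).

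**The case against.** Much can be said for the plan as written.

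- **The 19% drives nothing.** Neither 0.136 nor the 1400 households depends on it. Divided by the pooled coverage of the two arms (72.4%), 13.6 points is 18.8%, which rounds to 19%. The article describes no such base, so the figure still needs correction, but it is a minor slip.
- **The section already mentions end line.** That is true, but it never says that the planned estimator is a different one.
- **No shortfall is shown for the difference-in-difference.** This stands. A reader might infer from the upper end of the table that the trial is underpowered for its primary analysis. The documents do not support that. The planned model has a village intercept and no village-by-round term, which corresponds to r = 1 and about 11.1 points against control, better than the stated 13.6. The larger values rest on a correlation that the documents do not give.
- **A confidence interval interprets a null.** The Analysis section promises one for CLTS against CLTS+CG, and end-line data were collected in March and April 2024, so a new MDE alters no design decision. This limits the weight of the point. It does not make the published figure describe the analysis.
- **Percentage points only approximate the planned effect,** which is an odds ratio from a logistic model. This also stands.

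**Conclusion.** The point holds as a mismatch between the stated MDE and the stated analysis and objectives. The 0.136 is arithmetically right for what it is: one intervention arm against control, at end line, from 67%. It is not the MDE of the interaction, and nothing is stated for CLTS+CG v CLTS, where the end-line figure on the same inputs is 14.7 points.

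For the difference-in-difference, the MDE is about 11.1 to 19.0 points against control and 12.2 to 20.9 for CLTS+CG v CLTS. Whether the figure against control is better or worse than 13.6 turns on a between-round correlation of about 0.75. These ranges assume 67% in every cell except the treated arm at end line, ICC 0.1, households independent between rounds, and a normal approximation on the percentage-point scale.

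The observed baseline matters more in practice than the choice among these figures. If the primary outcome is coverage as the Sample Size section defines it, calculations that start from 67% no longer describe these villages.

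**What to change.** Rewrite the sample-size paragraph:

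1. Label 13.6 points as an end-line MDE for one intervention arm against control, and change 19% to 20.3%.
2. Add the MDE for the planned difference-in-difference, against control and for CLTS+CG v CLTS, over a stated range of between-round village correlation, and say which value the planned model implies.
3. Base these on the observed baseline (94.0% control, 96.3% CLTS+CG, 97.8% CLTS), and state that a 13.6-point rise is not attainable on the at-least-unimproved definition.
4. State that CLTS+CG v CLTS was not separately powered and will be interpreted from its confidence interval.

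The cost is one paragraph and a short recalculation. No additional households or data collection are needed.

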### Description of the Intervention

Households in TA Ntchema (CLTS only) will receive standard CLTS intervention plus government-delivered hygiene promotion. We refer to this arm as the CLTS group. Households in TA Chitera (CLTS+CG group) will receive the same combination of interventions as the CLTS group in addition to community-based CGs. We refer to this as the CLTS+CG group.

CLTS is the main sanitation intervention component for W4E and is implemented in line with the Malawi National Sanitation and Hygiene Strategy [29]. As part of W4E, relevant district technical officers and community leaders (also known as Natural Leaders) are responsible for implementing CLTS. Trained CLTS facilitators will conduct the triggering sessions that include participatory activities, such as the walk of shame, shit calculation, and community sanitation mapping. The purpose of these activities is to trigger behavioral emotions, such as shame and disgust so that community members understand the consequences of open defecation. If successfully implemented, triggering sessions have the potential to stimulate community members to stop open defecation and adopt improved sanitation practices, including the construction and effective use of latrine facilities. In addition to sanitation promotion, the project partners delivered hygiene promotion campaigns using pre-established sanitation and hygiene messages from the Ministry of Health in marketplaces and villages. This was achieved through 4 separate campaigns, each lasting 5 days, using a mobile van for message dissemination and distributing information leaflets.

In TA Chitera, in addition to the activities outlined above, households will receive visits from local CGs. CG leaders and cluster leaders support intervention delivery and local triggering sessions, specifically by facilitating CG meetings with CG households and conducting household follow-up visits. CGs are intended to extend the reach of CLTS behavior change messaging, providing additional points of contact with program households. CGs also participate in posttriggering follow-up visits to households to assess sanitation coverage and use.

In line with CLTS values, the W4E project does not intend to provide any latrine construction or hygiene facility materials or financial subsidies to households. It is the responsibility of the household owners to support themselves throughout the latrine and hygiene facility construction process.

### Selection of Clusters and Households

The primary sampling units (clusters) for the study are clusters (also called villages) and represent the units of W4E delivery for CLTS. Communities from the 3 participating TAs were randomly selected from a list of communities obtained from the Chiradzulu District Health Office. Inclusion criteria for the selected communities include that the community is in one of the 3 selected TAs that are part of the study area and have not yet received any exposure to the W4E project. Communities that were exposed to CLTS-related activities in the past 12 months and are outside the area of the 3 selected TAs are excluded from the study.

In early 2023, a list of all clusters in each study TA and their associated number of households was provided by the District Health Office. TA-specific median village size was calculated, and villages were categorized as either above or below the TA-specific median. Villages in each TA-specific above and below median list were ranked ordered according to a random number generated in Microsoft Excel and villages were enrolled sequentially until the necessary number of villages were enrolled. If a cluster could not be located or if the village chief did not provide permission for data collection, the next cluster on the rank order list was enrolled.

Households are the secondary sampling unit and individuals living in households in the study area are the primary study population. Twenty communities will be selected from TA Chitera (CLTS+CG), 20 from TA Ntchema (CLTS), and 30 from TA Nkalo (control). Among selected communities, a systematic sampling procedure (selecting every kth household) was used to select 20 households from each cluster included in the study. For each cluster, the population of households obtained from the District Health Office was divided by 20 (cluster sample size) to find the sampling interval (kth number). Then, the kth household was selected and included in the survey from any starting household chosen by an enumerator within the cluster.

### Data Collection

A baseline survey was conducted in all 3 TAs between May and June 2023 before intervention implementation in TA Chitera (CLTS+CG group) and TA Ntchema (CLTS group). An end-line survey was conducted in all 3 TAs between March and April 2024. TA Nkalo (control group) received the CLTS intervention after the end-line survey. A structured questionnaire with closed-ended questions with precoded responses on mobile devices on the KOBO collect platform (KoboToolbox) was used to collect data on household membership, wealth index, sanitation and hygiene facilities, and child health (Multimedia Appendix 2). Further, the enumerators conducted spot checks and recorded hygiene proxy measures, such as the presence and state of a latrine, presence, location, and type of handwashing facility (including the availability of soap and water). The interviews were conducted in Chichewa, the local language of Chiradzulu District. Chichewa-speaking enumerators with extensive training and expertise administered the structured questionnaire.

To confirm the availability of WASH infrastructure and hygiene practices, we conducted structured observations in 350 selected households (ie, 100 households from each intervention arm and 150 households from the control group) among the recruited 1400 households. A line listing of the 1400 households was created and a Microsoft Excel random generation number was run to identify the 350 households for observations. Specifically, the observations were intended to capture practices pertaining to the presence of latrine and handwashing facility with soap, handwashing practice at critical times (ie, before eating, before food preparation, after changing the child's nappy, and after latrine use), and child feces disposal. One observer was placed at each selected household. As behaviors of interest mostly occur in the morning hours to noon [31], observations lasted 4 hours from 8 AM to noon. The observer first conducted the structured observations after which he or she proceeded to administer the structured questionnaire.

### Data Management

Data collected using mobile devices was uploaded directly on the web to KOBO daily. Only the PI, coinvestigators, and study personnel with authorized access have access to web-based data. At the end of the data collection, the full dataset was uploaded into STATA (version 18; StataCorp) for analysis. Although no identifiable information was recorded during the surveys, study personnel will review the final database and permanently delete any identifiable information inadvertently collected during surveys. All data is stored on encrypted, password-protected servers.

### Study Outcomes

The primary outcome is sanitation coverage. Secondary outcomes include basic sanitation coverage, sanitation use, sanitation-related quality of life, latrine quality, presence of a handwashing facility, handwashing behavior, and safe disposal of child feces (Multimedia Appendix 3).

### Analysis

Statistical analysis will be carried out at the individual or household levels with appropriate adjustments for clustering within villages (and within households for individual-level outcomes). Data will be analyzed according to the TA and intervention assignment irrespective of whether the intervention was taken up fully, partly, or not at all. Since this is an effective study, only an intention-to-treat dataset will be maintained.

The primary estimates of the effectiveness of the intervention on primary and secondary outcomes will be based on a difference-in-difference analysis and models adjusted for design variables alone (TA, village population above or below TA-specific median); a fixed effect for village size (above or below the median) will be included in the model. All models will include a dummy variable for the treatment arm (ie, CLTS, CLTS+CG, or control) and data collection round (baseline and end line) as well as the interaction term of those 2 variables.

To account for the clustering of observations, hierarchical mixed-effects models will be used for all analyses. For household-level outcomes or outcomes where there is only one respondent per household, mixed effects models will account for clustering by including a random effect at the village level. For outcomes with multiple respondents or data points per household (specifically sanitation use, and hand washing behavior), an additional random effect will be added at the household level.

All analysis of primary and secondary outcomes will be based on the difference-in-difference approach. The regression coefficient of the interaction term between the treatment arm and the data collection round will be used as the primary effect measure. For binary outcomes measure, we will use melogit with robust SEs and regression coefficients exponentiated to estimate an odds ratio (OR). For continuous outcomes, we will use meglm, with identity link and Gaussian family.

The results will be presented with 95% CIs. Analyses will report on ORs and 95% CIs of each treatment arm compared to the control as well as the CLTS alone compared to CLTS+CG. Secondary outcomes include the following:

Sanitation use: measured as an individual-level binary indicator based on the reported location last time each member of the household used a latrine.Safe disposal of child feces: will be analyzed as a mixed effect model (household, village, and cluster) of observed household disposal sites of last defecation for all children under the age of 5 years.Basic sanitation coverage: this is a household-level indicator based on the presence of an observed sanitation facility that meets Joint Monitoring Programme (JMP) criteria for basic sanitation facilities, specifically an improved sanitation type.Sanitation-related Quality of Life (SanQoL-5): SanQoL-5 index is an individual-level variable reported by only one participant per household. It is a continuous variable (0-1) based on the weighted score of responses to 5 questions on a 3-level frequency scale [32].Latrine quality: latrine quality is a composite index based on observed and reported characteristics of household latrines [8]. Specific binary indicators will be combined using principal components analysis (PCA) and iteratively refined using standard approaches to index development. Outcomes will be analyzed as a continuous variable based on the PCA score.Basic handwashing facility: the presence of handwashing where both soap and water are available is a household-level binary variable. This will be analyzed in two ways: (1) both observed and reported handwashing facility (HWF) with both soap and water available at the time of data collection and (2) observed HWF with soap and water.Handwashing behavior: A binary outcome measure based on structured observation data. Structured observation data will be used to identify all predefined hand hygiene opportunities (eg, before food preparation, before eating, before feeding a child, after using a latrine, after cleaning a child, and after being in contact with an animal) and associated hand hygiene (0=no hand hygiene or hand hygiene with water only; 1=hands washed with soap). The analysis will be conducted at the event level with adjustment for repeated observations within the same household.

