### Study Design

The study design is a controlled before-and-after (CBA) trial with 2 treatment arms (each with 20 villages or clusters) and a control group (30 villages; Figure 2; Multimedia Appendix 1). CBA intervention designs are a nonrandomized approach used to evaluate the impact of interventions [26]. The advantages and disadvantages of the CBA study designs, also known as nonrandomized cluster-controlled trials, have been discussed elsewhere [27]. In this study, TAs are the unit of intervention assignment and villages (clusters) are the unit of analysis. [28] In our study, we selected 3 TAs (Figure 1) in Chiradzulu District, Malawi. TAs are 4th-level administrative units, with an average population of 34,000 in Chiradzulu [29]. Details on the program intervention are described below. For our trial, we selected 2 out of the 5 TAs scheduled to receive the full W4E intervention during the second year of program implementation to align with our implementation. We selected the 2 TAs with the closest match in population and estimated sanitation coverage from previous surveys. In discussion with program partners, one TA was assigned to receive the CLTS intervention, and one TA was assigned to receive the CLTS+Care Group intervention. We selected a third TA from the 3 TAs scheduled to receive the WASH for Everyone intervention in the third year of program activities as a control group for our study (Figure 2). The control TA was selected based on generally similar population and sanitation coverage measures and lack of contiguous borders with the 2 intervention TAs. TAs are the unit of intervention assignment for our study. Within each TA, villages serve as the specific study clusters which are the primary sampling units for data collection.

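### With 20, 20 and 30 villages and very few households lacking a facility, the robust-SE melogit intervals for the primary odds ratio are too narrow: nominal 95% intervals cover about 90-94%

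*Protocol article*

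**What the plan says.** The Study Outcomes section says "The primary outcome is sanitation coverage". The Sample Size section powers it on any facility at all: "the average percentage of households with at least unimproved sanitation coverage across Chiradzulu District was 67" per cent. Basic sanitation is a separate secondary outcome.

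The Analysis section fixes the method for household-level binary outcomes:
- Model and standard error: "For binary outcomes measure, we will use melogit with robust SEs and regression coefficients exponentiated to estimate an odds ratio (OR".
- Clustering: "mixed effects models will account for clustering by including a random effect at the village level".
- Effect: "The regression coefficient of the interaction term between the treatment arm and the data collection round will be used as the primary effect measure".
- Design term: "a fixed effect for village size (above or below the median) will be included in the model".
- Reporting: "Analyses will report on ORs and 95% CIs of each treatment arm compared to the control as well as the CLTS alone compared to CLTS+CG".

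The Study Design section describes "2 treatment arms (each with 20 villages or clusters) and a control group", the control group having 30 villages. Adjustment for Covariates makes the covariate-adjusted model the primary estimate. Multiple Comparisons makes no formal adjustment.

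**The concern.** A robust (sandwich) standard error clustered on village is justified when there are many villages and the outcome is not rare within arms. Neither holds comfortably here. Each contrast uses 40 or 50 villages, and on the any-facility measure the minority category is 2-6% of households, with nine households in the whole CLTS arm. In that setting the sandwich tends to be too small, and a normal critical value adds to the problem.

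At stake are the intervals and p-values for the primary outcome, in all three comparisons. An interval labelled 95% that covers less overstates the evidence, and nothing else in the plan absorbs the excess false positives.

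**Working it through.** **Inputs from the article**
- Sample Size: 20, 20 and 30 villages, 20 households per village per round, ICC 0.1, two-sided 5%, power 80%, coverage 67%.
- Table 2, no facility: control 36/600 = 6.0%, CLTS+CG 15/400 = 3.75%, CLTS 9/400 = 2.25%. Overall 60/1400 = 4.3%. Coverage is therefore 94.0%, 96.25% and 97.75%.
- Analysis: random-intercept logit with arm, round, arm x round and village size.

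**Assumptions not in the article**
- End-line rates equal baseline rates, so there is no effect.
- Robust means clustered on village.
- The shape of the village effect and its correlation across rounds are unknown, so both are varied.

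**Step 1: reproduce the plan's figure.** Design effect = 1 + (20 - 1) x 0.1 = 2.9. Effective sizes are 400/2.9 = 137.9 and 600/2.9 = 206.9. Take 67% against 80.58%:
- pooled proportion 0.724, null SE 0.04913, alternative SE 0.04694;
- 1.96 x 0.04913 + 0.8416 x 0.04694 = 0.1358.

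This matches the stated 0.136. It also shows that the plan's ICC of 0.1 is on the proportion scale.

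**Step 2: what ICC 0.1 means at 2-6% prevalence.** With a normal village effect on the logit scale, ICC 0.1 at 67% corresponds to a village SD of 0.74. Keeping that SD at the baseline rates gives proportion-scale ICCs of only 0.034 (control), 0.023 (CLTS+CG) and 0.015 (CLTS). Both readings are therefore shown.

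**Step 3: coverage of the nominal 95% robust interval.** The model was fitted by maximum likelihood, with a village sandwich (factor 70/69) and z = 1.96. The rows giving three values use 6,000 trials each, with simulation error of about 0.4 points. Values are in the order CLTS+CG v control, CLTS v control, CLTS+CG v CLTS.

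| Village effect | Coverage, % |
|---|---|
| ICC 0.1 on proportion scale, logit-normal, same in both rounds | 92.2 / 92.2 / 92.3 |
| Same, correlation 0.8 across rounds | 91.8 / 92.7 / 91.2 |
| Same, correlation 0.5 | 91.6 / 92.3 / 91.6 |
| ICC 0.1, beta-binomial, same in both rounds | 91.7 / 90.3 / 90.2 |
| ICC 0.1, beta-binomial, independent rounds | 92.6 / 91.7 / 91.8 |
| ICC 0.1 on the latent logit scale | 93.1-94.0 |
| Logit SD 0.74 carried over from 67% (about 3,000 replicates) | 92.6-93.8 |
| ICC 0.05, beta (about 3,000 replicates; rejection 6.9-7.7%) | 92.3-93.1 |
| No-facility rate halved at end line in both CLTS arms | 92.5-93.8 |
| Planned 67% coverage, ICC 0.1 | 93.8-94.3 |

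**Step 4: source of the shortfall.** In the first row the mean robust SE is 0.467 against an empirical SD of 0.514 (ratio 0.91), and 0.570 against 0.640 (ratio 0.89). The standard error is about 10% too small. A t critical value on 38 df is 2.024, and 2.024/1.96 = 1.03, so a t reference alone recovers only 3%.

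**Step 5: candidate remedies at the baseline rates, ICC 0.1**
- Ordinary robust SE with t on 38 df: 91.1-93.4%.
- Model-based SE: 95-96% if the village effect is constant across rounds, but 82-86% if it correlates 0.5.
- CR3-type sandwich (2,000 trials per scenario): 93.3-95.5% with z, 94.0-96.2% with t on 38 df.

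**Step 6: estimability.** In 0-1.2% of null trials, and 3.4% with halved rates, some arm-by-round cell has no household without a facility, so the odds ratio cannot be estimated.

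**The case against.** **The size depends on the ICC scale.** The article calls 0.1 conservative and pairs it with 67% coverage. Imposing a proportion-scale ICC of 0.1 at 2-6% prevalence implies much more village variation on the logit scale than the plan needed at 67%. This stands, and it is why the milder 92-94% belongs beside the 90-93%.

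**Stronger claims that a reader might infer are not supported.**
- Doubled false positives: coverage near 90% appears only for a stable beta-binomial village effect, and only in the two contrasts involving CLTS. The normal random effect that melogit itself assumes gives about 92%.
- Households without a facility clustering in a few villages: Table 2 gives arm totals only.
- CLTS+CG v CLTS being hit hardest: the ordering of the three contrasts changes between scenarios and mostly lies within simulation error.

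**The primary model was not tested.** The covariate-adjusted model was not fitted. This stands as a limit, although adding covariates does not correct a small-sample sandwich.

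**A small-sample correction may sit in an unseen analysis plan.** It may. But the article does fix the estimator and type of standard error, and the intervals that this choice gives as written are too narrow.

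**One TA per arm is the larger uncertainty.** That is a separate limitation. No village-level correction addresses it, and it does not make a miscalibrated interval acceptable.

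**Conclusion.** The concern holds at moderate size. At the baseline rates, the specified robust-SE intervals for the primary arm-by-round odds ratio cover about 90-93% with ICC 0.1 on the plan's own proportion scale, and about 92-94% under milder readings. Type I error is roughly 6-10%. Every scenario examined fell below 95%.

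The cause is few villages combined with a rare category: at the planned 67% the same method loses only about one point. The result assumes that the primary outcome is any facility, as in the Sample Size section, that rates stay near baseline, and that robust means clustered on village. It should not be read as a reason to abandon robust standard errors, because model-based ones do worse when village effects shift between rounds.

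**What to change.** In the Analysis section, keep the melogit interaction odds ratio and change only its inference. State that, for household-level binary outcomes, 95% intervals and p-values come from a bias-corrected sandwich clustered on village (leave-one-village-out jackknife or CR3), with t critical values on 38 df for 20 v 20 villages and 48 df for 20 v 30. Say explicitly that a t reference on the ordinary robust SE is not the chosen method.

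Add a village-level change analysis (end-line minus baseline proportion, one value per village, t reference) as a sensitivity check only. It targets a risk difference and drops the village-size term and the respondent- and household-level covariates, so it cannot replace the primary analysis. It does stay computable when an arm-by-round cell has no household without a facility.

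The cost is wording and modestly wider intervals. A guide to the severe end is the stretch that would calibrate the ordinary interval at rejection rates of 8.1% and 9.8%: 1.96/1.745 = 1.12 and 1.96/1.655 = 1.18, so about 12-18%. This is not a measured CR3 width, which may come out slightly larger in the most skewed setting. No new data are needed.
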